### ParaNASPP application (intervention group)

The intervention version of the application is a tool for scoring NIHSS. It facilitates direct communication and digital transfer of critical patient data to the on-call stroke physician in real-time. In addition to stroke symptom quantification by NIHSS, the application contains information on prehospital vital scores (blood pressure, pulse rate, blood glucose level and body temperature), history of antithrombotic medication use and time of onset. To make NIHSS applicable in a time-sensitive situation the ParaNASPP application is based on pictograms and short descriptive text to create a user-friendly guide to the examination of NIHSS (Fig. 3). This may also help standardising the NIHSS examination. The assessment sequence is fixed and concludes with a summary and overview image that provides a total score, an overview of all individual items scored, vital information and a direct contact option to the on-call stroke physician.

**Fig. 3 Fig3:**
[figure not shown]
Visualisation of main differences in prehospital ParaNASPP application

A separate study is conducted to compare stroke physicians scoring NIHSS in the application versus the original paper version. The results of this validation study will be published.

### ParaNASPP application (control group)

Paramedics in the control group access the control version of the application. An inclusion with this version registers suspected stroke cases. Patient assessment and communication with the on-call stroke physician are in agreement with standard procedure. This procedure entails FAST as a screening tool and communication with the on-call stroke physician through a direct telephone number. Figure 4 describes the patient flow and data collection in both control- and intervention groups.

**Fig. 4 Fig4:**
[figure not shown]
Screenshot from ParaNASPP application showing test for command

### In-hospital procedure

In the intervention group, a QR-code is scanned with an iPad in the ED in order to transfer prehospital data and opens for continuing in-hospital application registration. Otherwise, handover to the stroke team will be according to standard procedure. Patients included in the intervention group have their data registered on a dedicated iPad, and all subsequent NIHSS assessments completed in the ED and the SU will be registered on this device, as with information on radiological examinations and revascularisation therapy conducted. Remaining variables, such as past medical history, functional outcome and final diagnosis, are collected retrospectively from standard registrations in patient records.

Diagnostic assessment is based on the current procedure in the SU and completed by the senior ward physician at discharge. Acute stroke is defined as main or supplemental ICD-10 (International Classification of Diseases, version 10) diagnose code at discharge: I60 Non-traumatic subarachnoid haemorrhage, I61 Non-traumatic intracerebral haemorrhage, I63 Cerebral infarction, I67.7 Non-pyogenic thrombosis of the intracranial venous system, G45.3 Amaurosis Fugax, G45.8 Other transient cerebral ischemic attacks and related syndromes and G45.9 Transient cerebral ischemic attack, unspecified. All other discharge diagnoses are defined as stroke mimics (non-stroke).

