### ParaNASPP application

The ParaNASPP application is a mobile iOS application developed by the Norwegian Air Ambulance Technology. It is derived from a collaboration between neurologists, paramedics, researchers, graphic designers and app developers. The application was set out to digitalise the NIHSS assessment method and communication flow between the professionals, aiming to improve patient assessment and triage. It is a full-cycle solution including prehospital and in-hospital use, enabling ambulance car deployment, electronic medical record entry and securing data for scientific purposes. The application contains a full training module for digital learning and continued education of medical professionals. It keeps a high standard of engineering and security. The application is distributed through an enterprise master data management (MDM) solution to mobile devices in ambulances and hospitals. The access is limited to certified users only and uses a two-factor phone authentication and an employee-specific identification.

The application is installed on mobile phones of every participating ambulance, the on-call stroke physicians’ mobile phones and iPads in the SU and ED. Data collection prehospital is done by paramedics, in the ED by stroke physicians and by stroke nurses in the SU. All data registered in the application are automatically transferred to the University of Oslo, Services for sensitive data (TSD). The prehospital part of the application has both a control and an intervention version, with different functionalities (Table 1).

**Table 1 Tab1:** Functionality of ParaNASPP application

Application functionality	Control version	Intervention version	In-hospital version
Generation of study ID	X	X	
Registration of paramedic ID	X	X	
Ambulance trip ID (AMIS)	X	X	
Age	X	X	
Gender	X	X	
Onset of symptoms	X	X	
Delivery location	X	X	
COVID-19 status prehospital	X	X	
Antithrombotic medication		X	
NIHSS, individual elements and total score		X	X
Vital parameters registered—blood pressure, pulse rate, body temperature and blood glucose		X	X
Encrypted transfer of information to stroke physician via SMS		X	
Direct call through application to on-call stroke physician		X	
Generation of QR-code for transfer of data to in-hospital application		X	
QR-code scanner			X
Admission time			X
Time of imaging (CT, CTA, CTP, MRI			X
Time of IVT or EVT			X

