### Outcome measures

#### Primary outcome measure

The primary outcome measure is positive predictive value (PPV) for prehospital identification of patients with acute stroke. This will be calculated using study patients discharged with a stroke diagnosis (true positive) divided by all study patients seen by the stroke team (both true and false positive). Secondary outcomes are listed in Table 2.

**Table 2 Tab2:** Secondary outcome measures

Outcome measure	Cohort 1 Suspected stroke	Cohort 2 Final diagnosis of stroke
Prehospital on-scene time	X	X
Onset-to-hospital time	X	X
Onset-to-treatment time	X	X
Interrater agreement between paramedics and admitting stroke physician	X	X
Absolute change in NIHSS from prehospital to; admission, 2 h post admission, 24 h post admission and at discharge	X	X
Number of patients with suspected acute stroke admitted to the stroke unit	X	X
Number of patients with confirmed acute stroke diagnosis	X	
Door-to-(first) brain imaging time interval	X	
Number of patients receiving IVT	X	X
Door-to-needle time in patients receiving IVT	X	X
Number of patients with symptomatic post-thrombolysis haemorrhage	X	X
Number of patients receiving EVT		X
Door-to-groin-puncture time in patients receiving EVT		X
mTICI score		X
Door-to-needle time for blood pressure lowering in patients with ICH		X
NIHSS at discharge		X
NIHSS at 90-day follow-up		X
Modified Rankin Scale (mRS) at 90-day follow-up		X
Identified LVO, anterior and posterior		X
ASPECTs		X
Infarction volume (MRI/CTP)		X

*mTICI* modified thrombolysis in cerebral infarction [28], *ICH* intracranial haemorrhage, *ASPECTs* Alberta Stroke Program Early CT score [29]

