### Data monitoring and safety committee

A data safety committee carries out an interim analysis after activation of cluster 3. The committee reviews prehospital times and especially prehospital on-scene time. A significant increase in onset-to-hospital time is acceptable only if onset-to-needle time (i.e. door-to-needle time) is reduced.

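### As described, in-hospital admission, imaging and treatment times are captured in the app for intervention patients only, so data source appears to coincide with study arm for the door-based secondary outcomes

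*Protocol article*

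**What the plan says.** In the Protocol article, the In-hospital procedure section describes the route for one arm: "In the intervention group, a QR-code is scanned with an iPad in the ED in order to transfer prehospital data". This step "opens for continuing in-hospital application registration". It continues: "Patients included in the intervention group have their data registered on a dedicated iPad". The NIHSS scores taken later in the emergency department and stroke unit go onto the same device, "as with information on radiological examinations and revascularisation therapy conducted". There is no parallel sentence for control patients. Remaining variables, with medical history, functional outcome and final diagnosis as examples, are taken retrospectively from patient records.

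Table 1 (section ParaNASPP application) agrees with this. The row "Generation of QR-code for transfer of data to in-hospital application" is marked for the intervention version only. The rows for admission time, "Time of imaging (CT, CTA, CTP, MRI" and time of IVT or EVT are marked for the in-hospital version only. The section The ParaNASPP model restricts the control group's use of the app to registering suspected cases.

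Table 2 lists door-to-first-imaging time, "Door-to-needle time in patients receiving IVT" and door-to-groin-puncture time as secondary outcomes. The section Data monitoring and safety committee makes the acceptability of a longer onset-to-hospital time depend on a shorter time to needle, which it equates with door-to-needle time.

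**The concern.** A time interval can be compared between arms only if its start and end are recorded in the same way in both. If intervention patients' times come from an app completed by ward and emergency staff, and control patients' times come from the chart, any habitual difference between the two sources adds to the estimated intervention effect.

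The usual remedies do not help. A larger sample narrows the interval around the biased value. Hierarchical models with station and period terms cannot separate the two effects, because the source changes when each station crosses over. Multiple imputation, planned for variables with more than 5% missing, does not apply, because the values are present but measured differently.

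At stake are the door-based secondary outcomes and, through door-to-needle time, one input to the committee's interim judgement.

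**Working it through.** No stated figure bears on this point, so there is none to reproduce. The check is a comparison of the text by arm, followed by illustrations on assumed inputs.

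**Step 1. Capture route by arm**

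| Item | Intervention | Control | Where stated |
|---|---|---|---|
| QR code generated | Yes | No | Table 1 |
| QR scan opens in-hospital registration | Yes | Not described | In-hospital procedure |
| Imaging and revascularisation data on iPad | Yes | Not described | In-hospital procedure |
| Prehospital app used for | NIHSS, vital signs, communication, transfer | Registering the suspected case | The ParaNASPP model; Table 1 |
| Other source named | Patient records, for remaining variables | Patient records | In-hospital procedure |

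Records as the control source follow by elimination; the text does not name them for these times.

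**Step 2. How a source difference enters the estimate**

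Let δ_door and δ_end be the mean differences (app minus record) in the starting and ending times of an interval. Then:

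observed arm difference = true difference + (δ_end − δ_door)

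The bias is the net offset, minute for minute, whatever the sample size. It is negative if the app's door time runs late, positive if its needle or imaging time runs late, and zero if the two cancel or the entries are copied from hospital systems.

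Scale, on assumed inputs: with a net offset of 2 to 5 minutes and a door-to-needle time of 30 minutes, 2/30 = 7% and 5/30 = 17%, in either direction.

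**Step 3. Effect on a nominal 5% test**

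Assumed, not in the document: no true difference, independent patients, SD s of 15 or 25 minutes, and m patients per arm with both times available.

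SE = s√(2/m); d = offset/SE; rejection probability = Φ(d − 1.96) + Φ(−d − 1.96)

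Example with m = 100, s = 15 and offset 2: SE = 15√0.02 = 2.12, d = 0.943, so Φ(−1.017) + Φ(−2.903) = 0.156.

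| Net offset (min) | m = 100, SD 15 | m = 100, SD 25 | m = 200, SD 15 | m = 200, SD 25 |
|---|---|---|---|---|
| 1 | 7.6% | 5.9% | 10.2% | 6.9% |
| 2 | 15.6% | 8.7% | 26.6% | 12.6% |
| 5 | 65.4% | 29.3% | 91.5% | 51.6% |

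**Step 4. The committee's rule**

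Suppose the app's admission time is used as hospital arrival and runs late by δ. Onset-to-hospital time rises by δ and door-to-needle time falls by δ. Onset-to-needle time does not contain the door time and does not change. Because the rule equates the last two intervals, a door offset can reach it, but it acts on both sides of the condition.

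**The case against.** The strongest reply is that a difference between arms is inferred, not stated. Figure 4 is said to describe data collection in both groups and is not visible in the text at hand. The ParaNASPP application section says, without limiting it by arm, that stroke physicians and stroke nurses collect data in hospital, and that it is the prehospital part of the app that has two versions. Nothing says the in-hospital version cannot be opened without a QR code. The app is not said to stamp times automatically, so staff may copy the registered arrival time and the scanner time, in which case both arms share one clock. Table 1 has a field for IVT or EVT time but does not name groin puncture. The committee's stated focus is elsewhere: "The committee reviews prehospital times and especially prehospital on-scene time", which the iPad fields do not measure. Variable-level data sources are often left to a fuller document, and the outcomes concerned are three of 21 secondary outcomes.

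Much of this stands. A reader might infer that app times are entered live, that control times can come only from records, and that the resulting artefact favours the intervention. The document supports none of these as fact: it gives no entry timing, names no control source for these times, and gives no basis for the sign of an offset. A late needle entry would work against the intervention, and a late door entry would also lengthen onset-to-hospital time.

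The reply does not remove the arm-specific scheme itself. The article does more than omit a source: it says which arm's patients are registered on the iPad and limits the control app to registering cases. Followed as written, that ties source to arm.

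**Conclusion.** The point holds as a risk of confounding by measurement source, not as a demonstrated bias. It applies to door-to-imaging and door-to-needle time, and to door-to-groin-puncture time only if the app's EVT time is used as its end point. It could also affect the door-to-needle time in the committee's rule.

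The size and direction cannot be determined from the document. The illustrations show only that a few minutes would be enough to matter; the offsets, SDs, numbers per arm and 30-minute interval are all assumptions. If app entries are copied from hospital systems, the bias could be nil.

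The primary outcome, PPV based on discharge diagnosis, is unaffected. The conclusion rests on reading the In-hospital procedure section, Table 1 and The ParaNASPP model together, and would change if Figure 4 or the full protocol shows the same source in both arms.

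**What to change.** For every between-arm comparison of these intervals, including those given to the safety committee, take the times from one common source in both arms: hospital arrival registration for door, the imaging system for first imaging, and the patient record for needle and groin puncture. Use the app times only descriptively, and report their agreement with the record times in intervention patients, for example as the median difference.

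The cost is modest. Record times must also be extracted for intervention patients, but retrospective extraction from records is already planned for other variables. The comparison loses app times that may be finer than the chart. Recruitment, the intervention and the primary analysis do not change. If a common source is already in use, one sentence saying so settles the point.

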### Outcome measures

#### Primary outcome measure

The primary outcome measure is positive predictive value (PPV) for prehospital identification of patients with acute stroke. This will be calculated using study patients discharged with a stroke diagnosis (true positive) divided by all study patients seen by the stroke team (both true and false positive). Secondary outcomes are listed in Table 2.

**Table 2 Tab2:** Secondary outcome measures

Outcome measure	Cohort 1 Suspected stroke	Cohort 2 Final diagnosis of stroke
Prehospital on-scene time	X	X
Onset-to-hospital time	X	X
Onset-to-treatment time	X	X
Interrater agreement between paramedics and admitting stroke physician	X	X
Absolute change in NIHSS from prehospital to; admission, 2 h post admission, 24 h post admission and at discharge	X	X
Number of patients with suspected acute stroke admitted to the stroke unit	X	X
Number of patients with confirmed acute stroke diagnosis	X	
Door-to-(first) brain imaging time interval	X	
Number of patients receiving IVT	X	X
Door-to-needle time in patients receiving IVT	X	X
Number of patients with symptomatic post-thrombolysis haemorrhage	X	X
Number of patients receiving EVT		X
Door-to-groin-puncture time in patients receiving EVT		X
mTICI score		X
Door-to-needle time for blood pressure lowering in patients with ICH		X
NIHSS at discharge		X
NIHSS at 90-day follow-up		X
Modified Rankin Scale (mRS) at 90-day follow-up		X
Identified LVO, anterior and posterior		X
ASPECTs		X
Infarction volume (MRI/CTP)		X

*mTICI* modified thrombolysis in cerebral infarction [28], *ICH* intracranial haemorrhage, *ASPECTs* Alberta Stroke Program Early CT score [29]

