Several shortened stroke scales have been developed for prehospital use, though with lower sensitivity and specificity compared to in-hospital assessment with NIHSS [11]. Prehospital scales may consequently fail to recognise stroke symptoms. Among these scales is the much used face arm speech time (FAST) scale, which is prevailing in prehospital procedures in Europe [12], Norway included. A recent study has suggested that FAST is insufficient for prehospital triage since large vessel occlusions (LVO) may be FAST negative [13]. In addition, FAST leads to too many false negatives in strokes with posterior circulation origin [14]. NIHSS also has a lower sensitivity for posterior strokes, but assessment for ataxia and visual field are important additions compared to FAST [15]. In contrast, another study found existing prehospital stroke scales to have acceptable diagnostic accuracy for identifying LVOs [16], though NIHSS is better, in comparison, at predicting LVOs [17]. However, a minority of stroke patients have LVOs [18]. A better stroke identification tool is thus recommended for prehospital providers [19]. By introducing the digital ParaNASPP platform with prehospital NIHSS we hope to establish a common language for stroke identification, standardise the prehospital assessment and provide a continuous evaluation through the chain of treatment.

An overtriage is currently necessary to achieve high treatment rates and is considered acceptable and cost-beneficial up to 30% [20, 21]. Further overtriage puts strain on both the pre- and in-hospital systems and delays correct treatment for stroke mimic conditions. In contrast, about a third of acute stroke patients are not identified in the prehospital setting [11, 19] which represents a highly problematic undertriage.

The study aims to explore whether ParaNASPP-trained paramedics using a mobile application with NIHSS and digital communication may improve triage of acute stroke patients and ensure standardised transfer of critical patient data to the in-hospital stroke physician. The intervention will be compared to paramedics using standard procedure with FAST and communication through regular channels. We hypothesise that the number of patients brought to the emergency department (ED) with suspected acute stroke and discharged with a stroke diagnose is significantly higher in the ParaNASPP model (intervention) compared to standard prehospital model (control).

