### Study population

The inclusion criteria are met if a paramedic suspects acute stroke in a conscious, adult patient with stable vital signs. After an initial assessment, a focused medical history and physical examination is obtained. If the patient’s symptoms are compatible with acute stroke based on the clinical understanding of the paramedic, the on-call stroke physician will be contacted. Patients accepted to the OUH stroke team are formally included in the study. Written informed consent will be obtained from the patients or their next of kin for their anonymised participation in the study. If possible this is obtained during hospitalisation by members of staff at the Stroke Unit (SU), otherwise retrospectively by the research team (see Additional file 3). The ParaNASPP application (see Additional file 2) registers data every time it is used, also when the paramedic or stroke physician no longer suspects an acute stroke, but these patients are not included. Patients that are either pregnant, imprisoned or seen by a physician prior to ambulance transport to the hospital, will be excluded. Inclusion to the study depends on adherence to procedures. During the study period, there is a focus on information, team availability and follow-up to ensure study inclusion after protocol.

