### The ParaNASPP model

Paramedics in the control and intervention clusters receive different levels of training. The intervention paramedics are trained in general stroke knowledge and assessment of acute stroke patients using NIHSS. NIHSS is scored using a mobile application that also provides direct communication through the application with the on-call stroke physician. The intervention comprises of NIHSS providing a standardised communication and an electronic transfer of data to the hospital upon arrival. In the control group, no specific training is provided. The mobile application is only used for the registration of suspected stroke patients, and the required conference with the on-call stroke physician is made by an ordinary telephone call.

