### Statistics

We will present continuous data as mean (standard deviation) for symmetrical data, and median (quartiles) for skewed data. Categorical data will be presented as absolute numbers and percentages. Classical parametric and non-parametric statistical tests will be used to compare differences between the intervention and control groups as appropriate.

PPV will be calculated with 95% confidence intervals (CI) and used for statistical testing and comparison between groups. This comparison will be performed primarily on the total number of patients included, but adjustments for the temporal inclusion design using hierarchical models will also be explored. The stepped wedge design allows for investigation into potential temporal trends, and subgroup analysis will be done to compare PPV (CI) for the various clusters and time periods using appropriate linear and non-linear curve fitting models.

A modified Rankin Scale (mRS) shift analysis to assess discharge and 90-day functional outcomes [25] will be performed. mRS will be analysed both as an ordinal scale (0–6) and as a dichotomised variable where mRS 0-2 defines a favourable outcome. As shown in Table 2, a certain analysis will only be considered for a subgroup population.

Statistical analysis will be performed in Stata and R.

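### Cohort 2 is formed through steps that the intervention is meant to change, so two-group tests of its mRS, NIHSS and time outcomes mix any effect with case mix and calendar time

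*Protocol article*

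**What the plan says.** Entry has two steps (Study population). If the symptoms are "compatible with acute stroke based on the clinical understanding of the paramedic, the on-call stroke physician will be contacted". Then: "Patients accepted to the OUH stroke team are formally included in the study".

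The intervention acts on both steps. On the first, "The intervention paramedics are trained in general stroke knowledge and assessment of acute stroke patients using NIHSS" (The ParaNASPP model). On the second, Table 1 shows that only the intervention version of the application records NIHSS, vital parameters and antithrombotic medication and sends information to the stroke physician.

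Table 2 then splits the secondary outcomes between suspected stroke (Cohort 1) and "Cohort 2 Final diagnosis of stroke". The 90-day mRS, discharge and 90-day NIHSS, and door-to-groin-puncture time are listed for Cohort 2 only. On-scene, onset-to-hospital, onset-to-treatment and door-to-needle (thrombolysis) times are listed for both cohorts. The stroke definition under In-hospital procedure includes TIA codes (G45.3, G45.8, G45.9), so Cohort 2 runs from TIA to haemorrhage.

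On method, the Statistics section says: "Classical parametric and non-parametric statistical tests will be used to compare differences between the intervention and control groups as appropriate". A shift analysis covers mRS at discharge and 90 days, and "mRS will be analysed both as an ordinal scale (0–6) and as a dichotomised variable where mRS 0-2 defines a favourable outcome". The only adjustment named is a hierarchical model for the temporal design. It appears in the PPV paragraph and is to be explored.

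**The concern.** Cohort 2 is defined after allocation, by steps that the intervention is built to alter. The Background expects the stroke set to change: it hypothesises that "the number of patients brought to the emergency department (ED) with suspected acute stroke and discharged with a stroke diagnose is significantly higher" under the intervention, says that about a third of strokes are not identified before hospital, and says of NIHSS that "assessment for ataxia and visual field are important additions compared to FAST". If the added strokes differ in severity from those already found, functional outcome and treatment times will differ between phases even if no patient's outcome changes. A two-group test cannot separate the two.

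The second problem is time. In a stepped wedge the intervention comes later by construction, so a pooled comparison also absorbs any drift in care or referral.

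At stake is the reading of the trial's patient-outcome results. The primary PPV comparison is not part of this point.

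**Working it through.** **The plan's own figures.** Sample size calculation gives 700/1800 = 38.9%, rounded to 40%, and a 10% increase, with 808 patients in total at two-sided 5% and 80% power. A two-proportion formula with continuity correction gives 2 × 408 = 816 for 40% v 50%, and 2 × 406 = 812 for 38.9% v 48.9%. Both are close to 808. A relative increase (40% to 44%) would need 4778, so the 10% is absolute. PPVs of 40% and 50% are therefore used below.

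**How many strokes could be added.** The planned total is 1300. An equal split of 650 per phase is an assumption.
- Control: 0.40 × 650 = 260 strokes.
- Intervention: 0.50 × 650 = 325 strokes.
- Added: 325 - 260 = 65, or 65/325 = 20% of intervention Cohort 2.

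This is an upper illustration, because holding acceptances at 650 forces the whole PPV gain to come from extra strokes. If only mimics fall, from 390 to 260, then 260/520 = 50% and no strokes are added.

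**Effect on mRS 0-2 with no true effect.** All rates here are assumed. Let g_m and g_s be the proportion with mRS 0-2 in mild and severe strokes, m the mild share in control, and s the mild share among the added strokes. Then

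spurious difference = (added share) × (g_m - g_s) × (s - m).

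| g_m / g_s | m | s | Control | Intervention | Difference | Rejection at 5% |
|---|---|---|---|---|---|---|
| 0.80 / 0.40 | 0.5 | 1 | 60.0% | 64.0% | +4.0 | 17% |
| 0.80 / 0.40 | 0.5 | 0.5 | 60.0% | 60.0% | 0 | 5% |
| 0.80 / 0.40 | 0.5 | 0 | 60.0% | 56.0% | -4.0 | 16% |
| 0.75 / 0.30 | 0.5 | 1 | 52.5% | 57.0% | +4.5 | 19% |
| 0.75 / 0.30 | 0.6 | 0 | 57.0% | 51.6% | -5.4 | 26% |

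For the last row, 0.20 × 0.45 × (0 - 0.6) = -0.054. The last two rows are the extremes over g_m 0.70-0.80, g_s 0.30-0.40 (three pairs tried), m 0.5-0.6 and s 0-1. Rejection is for an unadjusted two-sided test on 260 v 325 patients, ignoring clustering.

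**Time.** Five stations and six 12-week periods, with one station crossing over per period, give control counts of 5, 4, 3, 2, 1, 0 and intervention counts of 0, 1, 2, 3, 4, 5 station-periods, 15 each.
- Mean control period: (1×5 + 2×4 + 3×3 + 4×2 + 5×1)/15 = 35/15 = 2.33.
- Mean intervention period: (2×1 + 3×2 + 4×3 + 5×4 + 6×5)/15 = 70/15 = 4.67.

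The gap is 2.33 periods × 12 = 28 weeks of recruitment time. The pause of almost seven months in 2020 (Trial status) widens it in calendar time.

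**The case against.** - **The text is silent on severity adjustment; it does not exclude it.** The tests are to be used as appropriate, no model is named for the shift analysis, and covariates for secondary outcomes often sit in an analysis plan that is not shown. This stands: a reader might infer that the protocol rules out severity adjustment, and it does not. But the cohort and the class of test are stated, and choosing among classical two-group tests removes neither selection nor time.
- **The direction is unknown.** A reader might infer that the added strokes are milder, so that the intervention will look beneficial. With 50% favourable among the common strokes and 80% among the added ones, (260 × 0.5 + 65 × 0.8)/325 = 56% v 50%. The documents do not support that as a forecast. They do not say that posterior strokes are milder, and the Background notes that NIHSS too has lower sensitivity for them.
- **PPV can rise without more strokes.** The abstract's Discussion names fewer mimics as a route, and recruitment ends at 72 weeks whatever the group sizes. This stands, so zero bias belongs in the range. The hypothesis of more stroke-diagnosed patients still makes some change plausible.
- **Selection occurs before Cohort 1 is formed.** This is correct, and it means that moving the outcomes to Cohort 1 would not help.
- **These are secondary outcomes, and Limitations already admits that false negatives cannot be determined.** Both are true, but Limitations draws no consequence for the Cohort 2 comparisons.

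**Conclusion.** The point holds as a matter of interpretation and analysis. Between-phase comparisons of mRS, NIHSS and times in Cohort 2 are conditional on suspicion, acceptance and diagnosis. The first two are targets of the intervention, and the stepped-wedge order confounds the comparison with calendar time. The bias has unknown sign and size: zero if Cohort 2 is unchanged or the added strokes have the control case mix, and -5.4 to +4.5 points in mRS 0-2 under the assumptions above. Those figures rest on a 650/650 split, on the full PPV gain coming from added strokes, and on assumed severity and mRS rates that the documents do not give. They show that a few points either way are possible, not that any particular artefact will occur. Nothing here shows that the trial will report a false benefit.

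**What to change.** For between-phase comparisons of the mRS, NIHSS and time outcomes, replace the classical tests with regression models that include station, calendar period and age: proportional odds for mRS, and a suitable model for times. Counts and interrater agreement need no such change.

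Report age and admission NIHSS by phase so that a shift in case mix can be seen. Fit a model adjusted for admission NIHSS only as a sensitivity analysis, and only if admission NIHSS comes from the same source in both phases. In-hospital procedure describes iPad registration for intervention patients, so the control source must be named. Note that admission NIHSS is measured after the prehospital intervention, so adjusting for it may remove part of a real effect. Prehospital NIHSS cannot serve, because the control version of the application does not record it (Table 1).

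State in the protocol and the report that these contrasts are conditional on acceptance and diagnosis and are not randomised comparisons of patient benefit.

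The cost is modest extra analysis, wider intervals from period adjustment with only five stations, and a more cautious reading of the secondary outcomes. Age and models for station and calendar period do not remove selection on severity, which is why the statement is needed as well.
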